## Abstract

**Background:**

Severe mental illness (SMI) is associated with substantial barriers to competitive employment, including stigma, cognitive impairments, and limited social support. The Individual Placement and Support (IPS) model is an evidence-based intervention that provides individualized assistance for job search, placement, and retention. Although IPS has shown effectiveness in high-income countries, there is limited evidence regarding its feasibility and preliminary outcomes in low- and middle-income settings, particularly in Latin America.

**Methods:**

This pilot randomized controlled trial will assess the feasibility of implementing the IPS model for adults with SMI in Jalisco, Mexico. We will recruit 120 participants who are actively seeking employment and randomly assign them to either the IPS intervention or a control group receiving standard employment services. The intervention includes tailored support from trained IPS Employment Specialists in resume building, interview preparation, job search, and follow-up after job placement. Primary feasibility outcomes include recruitment and retention rates, participant acceptance, implementation fidelity, and identification of contextual barriers and facilitators. Secondary outcomes will explore employment status at 12 months, financial well-being, and health-related outcomes.

**Discussion:**

Findings from this pilot study will contribute to addressing the current gap in implementation research on IPS in Latin America. Findings will offer preliminary insights into the feasibility, acceptability, and contextual adaptability of the model in a public mental health setting. These results are expected to guide the refinement of study procedures and support planning for a future definitive trial. Additionally, exploratory data on employment and quality of life outcomes may help identify relevant domains for further investigation.

**Trial registration:**

ClinicalTrials.gov NCT06019247. Registered on August 31, 2023.

## Introduction

### Background and rationale

Severe mental illness (SMI) limits access to competitive employment due to persistent stigma, cognitive challenges, and reduced social support. Employment has been associated with improved quality of life, self-esteem, and social integration among individuals with SMI, as well as reductions in symptom severity, hospitalization rates, and mental health service costs [1]. The Individual Placement and Support (IPS) model is a structured, evidence-based approach to supported employment that offers individualized assistance for job search, placement, and retention. Its core principles and operational components are outlined in Table 1 [2].

**Table 1 Tab1:** Principles and practices of the Individual Placement and Support (IPS) model

Principles	Practices
Competitive Employment: Agencies providing IPS are committed to regular jobs in the community as an attainable goal for clients seeking employment	Job Search and Placement: IPS Employment specialists assist clients in identifying job opportunities, preparing resumes, practicing interview skills, and applying for jobs
Zero Exclusion: Every client who wants to work is eligible for services regardless of “readiness”, work experience, symptoms, or any other issue	Initial Assessment and Vocational Profile: An initial assessment gathers information about the client’s work history, skills, interests, and preferences to guide the job search and placement process
Attention to Clients’ Preferences: Services align with clients’ choices, rather than practitioners’ expertise or judgments; IPS Employment Specialist help clients find jobs that fit their preferences and skills	Worker Preferences: Services are based on each job seeker’s preferences and choices, ensuring alignment with the individual's career goals and personal interests
Rapid Job Search: IPS programs help a client look for jobs soon after he/she expresses interest in working, rather than providing lengthy pre-employment assessment, training, and counseling	Immediate Job Search Initiation: Job searches begin within 30 days of program entry to minimize delays and ensure timely job application processes
Targeted Job Development: Based on clients’ interests, IPS Employment Specialist build relationships with employers through repeated contact, learning about the business needs of employers, and introducing employers to qualified job seekers	Systematic Job Development: IPS Employment Specialist visit employers to learn about their business needs and match them with clients' interests and skills
Integration of Employment Services with Mental Health Treatment: IPS programs closely integrate with mental health treatment teams	Integrated Services: IPS Employment specialists work as part of mental health treatment teams to provide coordinated care and comprehensive support
Personalized Benefits Counseling: IPS Employment Specialist help clients obtain personalized, understandable, and accurate information about how working may impact their disability insurance and other government entitlements	Benefits Planning: IPS Employment Specialist provide accurate information about Social Security, Medicaid, and other entitlements to help clients make informed decisions
Individualized Long-Term Support: Follow-along supports, tailored for the individual, continue for as long as the client wants and needs them to keep a job or advance career opportunities	On-the-Job and Follow-Along Support: Continuous, individualized support is provided to help clients retain employment and advance in their careers

Studies in high-income countries consistently report higher employment rates among IPS participants, typically around 55%, with some trials showing rates above 60% compared to standard vocational services [3]. However, there is limited evidence on IPS implementation and outcomes in low- and middle-income countries (LMICs), especially in Latin America. Regional studies highlight structural disadvantages among individuals with SMI in this region, including poverty, unemployment, interrupted education, and exposure to trauma and violence [4–6].

In Mexico, mental health care for people with SMI is often fragmented and misaligned with evidence-based practices [7]. The Jalisco public mental health system is a notable exception. It includes the Center for Comprehensive Care in Long-Stay Mental Health, the state’s largest psychiatric facility, which provides primary care, pharmacological treatment, and psychosocial rehabilitation [8]. However, existing employment services are generally lower in intensity and do not incorporate key IPS components, resembling services offered in other LMIC urban settings [9].

Recent reforms in Jalisco offer a favorable context for implementing and testing IPS. First, state legislation now guarantees the right to community-based mental health care, including free public access for individuals with SMI [10]. Second, a network of community-based services has expanded to include employment-oriented psychosocial rehabilitation activities [8]. Third, the National Employment Service supports a labor inclusion strategy targeting job seekers with psychosocial disabilities, in line with anti-discrimination laws and labor policy frameworks [11].

We propose a pilot study to explore context-informed adaptations of the IPS model and its implementation for people with SMI in Jalisco, Mexico, using an explanatory sequential mixed-methods design embedded within a pilot randomized controlled trial. Quantitative and qualitative data will be collected across phases to assess feasibility, fidelity, and contextual implementation barriers [12]. Findings from this pilot will contribute to the design of a future definitive trial and offer preliminary insights that could inform future research on the adaptation of employment support services in Mexico and other LMICs.

### Aims and objectives

The primary aim of this pilot randomized controlled trial is to evaluate the feasibility and contextual fit of an adapted version of the Individual Placement and Support (IPS) model for people with serious mental illness (SMI) within the Jalisco mental health system in Mexico. The specific objectives are:To adapt the IPS model to the Jalisco context, based on input from stakeholders including policymakers, service providers, users, and employers. This process will identify contextual barriers and inform modifications to IPS materials, delivery format, and fidelity criteria. The adapted model will be implemented through blended training (virtual and in-person sessions, e-learning resources).To assess the feasibility of implementing the adapted IPS model, including recruitment and retention rates, acceptability among stakeholders, and fidelity of delivery. Qualitative data will be collected to explore perceived facilitators and barriers to implementation.To explore preliminary outcomes related to employment, financial well-being, and health among participants. Outcomes will be compared between intervention and control groups at baseline, 6 months, and 12 months.To evaluate implementation processes and resource needs, including patterns of participation and fidelity over time, multilevel barriers and facilitators (e.g., at the provider and system level), and resource requirements (e.g., personnel, time, and infrastructure) for potential scale-up.

### Trial design

This mixed-method pilot randomized controlled trial (RCT) will evaluate the feasibility and contextual fit of an adapted IPS model for individuals with SMI in the Jalisco mental health system. We apply the Dynamic Adaptation Process (DAP) model [13], an implementation science framework that allows for structured, iterative adaptations to evidence-based practices while maintaining fidelity to their core components. The four phases of the study—Preparation, Adaptation, Implementation, and Evaluation—reflect the DAP structure and inform the sequencing of study activities to guide IPS adaptation and implementation, assess fidelity, and identify contextual barriers and facilitators.

We will evaluate the implementation and preliminary outcomes of the adapted intervention through a pilot randomized controlled trial (*N* = 120). This study includes quantitative and qualitative assessments at baseline, 6, and 12 months, involving participants (e.g., employment, financial well-being), providers (e.g., attitudes towards evidence-based practices), and other key stakeholders (e.g., potential employers). This design addresses the primary aim and specific objectives described above by allowing us to examine implementation processes, explore patterns of employment and health-related outcomes, and generate estimates needed to plan a future regional trial in Latin America.

Prior experiences with IPS adaptations in other countries and marginalized populations in the USA (e.g., Latinxs, individuals experiencing homelessness) [14, 15]—together with insights from the local Mexican labor market—inform our adaptation strategy. We completed initial interviews and focus groups with stakeholders as described below.

IPS implementation follows four DAP phases: preparation, adaptation, implementation, and evaluation (Fig. 1). Collaborators in the USA have used a similar approach to deliver other evidence-based programs in Latin America, such as OnTrack Chile (1U01MH115502-01) [16]. This iterative process integrates ongoing experience to refine adaptations. We engage multiple stakeholders (e.g., policymakers, providers, participants, and employers) to discuss contextual factors within and beyond mental health services and identify potential adaptations to the IPS curriculum. Once the trial begins, ongoing training will involve in-person meetings and e-learning modules. We will apply mixed-methods to assess fidelity, service delivery patterns, contextual barriers and facilitators, and estimated implementation costs. The specific objectives, outcomes, methods, and expected outputs for each phase are summarized in Table 2.

**Fig. 1 Fig1:**
[figure not shown]
Phased implementation strategy for the adapted IPS model guided by the Dynamic Adaptation Process (DAP). The diagram illustrates the study’s four phases—Preparation, Adaptation, Implementation, and Evaluation—each with its corresponding activities. The Evaluation phase includes assessment of feasibility outcomes (recruitment, retention, and participant acceptance), as well as implementation fidelity, contextual barriers, and pilot outcome measures. Stakeholder engagement at all levels informs adaptations and supports continuous refinement of the IPS model

**Table 2 Tab2:** Study phases, objectives, implementation outcomes, methods, and expected outputs

Phase	Objective	Implementation outcome(s)	Methodology	Expected outputs
Preparation	Understand contextual barriers and assess readiness	Organizational readiness	Semi-structured interviews, focus groups	Matrix of barriers and facilitators
Adaptation	Tailor IPS model while preserving fidelity to core components	Contextual fit, fidelity	Stakeholder meetings, material review, iterative feedback	Adapted IPS materials; training and supervision plan
Implementation	Deliver IPS model with fidelity in routine services	Fidelity, acceptability	IPS service delivery; fidelity assessment; training logs	Fidelity reports, training logs, implementation notes
Evaluation	Assess feasibility and inform the design of a future trial	Feasibility, retention, acceptance	Pilot RCT; follow-up interviews and focus groups	Descriptive statistics; thematic analysis reports

## Methods: participants, interventions, and outcomes

### Study setting

The study takes place in the Jalisco public mental health system, as previously described [8], which integrates community-based services and offers a structural foundation for implementing and testing the IPS model in a real-world context. This setting engages multiple stakeholders, including policymakers, healthcare providers, service users, employers, and the National Employment Service. These actors contribute to the adaptation and delivery of the IPS model, aligning it with local needs and service structures.

The National Employment Service brings expertise in employment access for people with disabilities, including those with mental health conditions [10], and supports participant job placement efforts. The setting provides the institutional infrastructure and community reach required to assess the feasibility of the IPS model in a Latin American public health system. Findings may inform future implementation planning in similar contexts.

### Eligibility criteria

Participants are eligible if they are at least 18 years old and have a diagnosis consistent with SMI, including schizophrenia spectrum disorders, bipolar I disorder, major depressive disorder with severe functional impairment, or other psychotic disorders. Diagnoses will be made by the treating psychiatrist at the Center for Comprehensive Care in Long-Stay Mental Health as part of routine clinical evaluation. No symptom severity cut-offs will be used for eligibility; instead, SMI will be determined based on the presence of a persistent psychiatric disorder associated with substantial functional impairment in daily activities. This approach is consistent with international definitions of SMI and with current clinical practice at the study site. Additional eligibility criteria include expressing a goal of obtaining paid, competitive employment, attending two informational sessions prior to recruitment, having no competitive employment in the past 3 months, being available to participate in the study for 1 year of follow-up, and providing informed consent.

### Interventions

#### Explanation for the choice of comparators

Treatment as usual (TAU) for individuals with SMI at the Center for Comprehensive Care in Long-Stay Mental Health is delivered by a multidisciplinary team composed of two full-time psychologists, two full-time social workers, a part-time occupational therapist, and a part-time psychiatrist. This team maintains connections with various public and private organizations that assist in job placement for individuals with mental disabilities, including cooperatives. The positions offered through these channels are generally categorized as non-competitive or self-employment activities, such as broom-making, craft-making, or gardening.

In addition to vocational support, the treatment team provides psychiatric medication, individual and group psychotherapy, and psychoeducation for both clients and their families. They also serve individuals with other mental health conditions, including substance use disorders. Vocational services offered in this setting are less intensive than those delivered through the IPS model and do not incorporate its core components. Furthermore, usual care is not guided by a standardized manual, protocol, or fidelity framework.

Usual care (TAU) was selected as the comparator because it represents the standard level of vocational and mental health services currently available in the Jalisco public mental health system. TAU is the ethically appropriate comparator given that no evidence-based supported employment model is routinely implemented in this setting. Using TAU allows evaluation of the added value of IPS within a real-world system and aligns with recommendations for pilot and feasibility trials of IPS in low- and middle-income countries, where comparisons with existing services enhance external validity. Furthermore, prior IPS trials in Latin America and other LMIC regions have relied on TAU as the primary comparator, making this choice consistent with international methodological practice.

#### Criteria for discontinuing or modifying allocated interventions

Participation in the study is voluntary, and participants may withdraw at any time without penalty. The intervention may also be temporarily paused or discontinued if the clinical team determines that continued participation is not advisable due to acute deterioration or circumstances that interfere with study procedures. These decisions will be made in coordination with the participant’s usual clinical providers.

Although measures are in place to safeguard data privacy and confidentiality, there remains a potential risk of unauthorized disclosure. To minimize this risk, the study will adhere to strict data protection protocols and ensure that research interviewers remain blinded to group assignment.

#### Risk and risk management

Participants will be adults with SMI receiving community-based services; therefore, some level of clinical and psychosocial risk is expected. A structured risk management protocol will be implemented to ensure participant safety throughout the trial. All IPS Employment Specialists and research staff will be trained to identify warning signs related to clinical deterioration, including increased symptoms, functional decline, suicidal ideation, or psychosocial crises.

If a participant reports suicidal thoughts, expresses intent, or presents significant behavioral changes suggesting elevated risk, the IPS Employment Specialist will pause all study-related activities and immediately activate the clinical escalation protocol. This protocol includes: (1) notifying the participant’s treating psychiatrist or mental health provider; (2) conducting a brief safety check using established procedures from local mental health services; and (3) coordinating a same-day clinical evaluation when indicated. In emergency situations, specialists will contact emergency services according to institutional guidelines.

Study participation may be temporarily paused or discontinued if the participant experiences acute psychiatric decompensation, requires hospitalization, or if the clinical team determines that continued involvement poses an unacceptable risk. All risk events and procedures will be documented and reviewed by the Research Adaptation Team and the site’s clinical supervisors to ensure consistent application of risk management procedures. The protocol prioritizes continuity of clinical care, and all participants will remain within their routine mental health services regardless of trial involvement.

#### Strategies to improve adherence to interventions

High adherence to the intervention is expected due to the structured nature of the IPS model, which allows for contextual and individual-level adaptations. Adherence will be monitored by IPS experts from the USA and the research team in Mexico, who will collaborate to ensure fidelity to the model while tailoring implementation to the local context in Jalisco. One of the IPS trainers is Spanish-speaking, facilitating direct support to local staff. To monitor compliance, the study will utilize structured tools, including activity logs, monthly implementation reports, and periodic assessments using an IPS fidelity scale.

#### Relevant concomitant care permitted or prohibited during the trial

Participants in both study arms will continue to receive standard mental health services at the Center for Comprehensive Care in Long-Stay Mental Health. These services are delivered by a multidisciplinary team including psychiatrists, psychologists, social workers, occupational therapists, and nurses. Standard care includes psychiatric medication, individual psychotherapy, and psychoeducation primarily focused on clients and family members. It does not incorporate the individualized, recovery-oriented components characteristic of the IPS model.

#### Provisions for post-trial care

Participants will continue receiving their usual clinical care at the Center for Comprehensive Care in Long-Stay Mental Health after the study concludes. No study-specific treatments will be withdrawn at the end of the trial, and no additional risks are expected following participation. As this is a minimal-risk study, no post-trial compensation or ancillary care is required. Participants will remain connected to their regular clinical teams, who will provide ongoing care as clinically indicated.

#### Outcomes

This study will assess feasibility outcomes related to the implementation of the IPS model and explore its preliminary effects on participant employment, financial well-being, and health-related outcomes. The evaluation will emphasize feasibility outcomes, while participant-centered outcomes will provide additional insight into the model’s potential impact. Data will be collected at baseline and through quarterly follow-up interviews. All instruments will be administered in Spanish; if no validated Spanish version exists, the measure will be translated using forward–back translation by bilingual specialists, followed by expert panel review to ensure conceptual equivalence and linguistic clarity. Table 3 provides a detailed summary of all planned outcomes and associated measures.

**Table 3 Tab3:** Outcomes and measures

Measure	Data Source	Interval (duration)	Constructs Addressed
Baseline participant interview	Participant	Baseline (45–60 min)	- Demographics (age, sex, gender, marriage status, race/ethnicity)—employment history (past year and past 5 years)—income history (annual income, income sources)—Housing history (past 5 years)—health service utilization history (past-year hospitalization and emergency service utilization, regular medical care)—health and functionality (Brief Psychiatric Rating Scale (BPRS), Medical Outcomes Study Short-Form 12-Item (SF-12, mental and physical), Social Occupational Functioning Scale (SOFS), Recovery Assessment Scale (RAS-24)—Social capital (numbers, education, and justice system involvement of parents, siblings, children, and friends)—Justice system involvement (arrest, incarceration, and conviction history)
Quarterly employment interview	Participant	Quarterly (10 min)	- Past-quarter employment (any competitive employment; per-job weeks worked, hours worked per week, hourly wage, job start/end dates if applicable)
Follow-up participant interview	Participant	6, 12 months (40–50 min)	- Housing (past 6 months)—health service utilization (past 6 months hospitalization and emergency service utilization)—health and functionality (Brief Psychiatric Rating Scale (BPRS), Medical Outcomes Study Short-Form 12-Item (SF-12, mental and physical), Social Occupational Functioning Scale (SOFS), Recovery Assessment Scale (RAS-24)
IPS Participation Measure	IPS Employment Specialist	Monthly (5–10 min)	- Observed participant: past-month competitive employment status (employed/not employed)—past month participation in IPS services (yes/no)—IPS activities participated in—past-month contact with IPS team (yes/no)—reasons for being either out of contact or not participating in IPS services—qualitative: difficulties encountered engaging participant or working with employers
Employment Specialist Service Log	IPS Employment Specialist	Monthly (5–10 min)	- IPS Employment Specialist past-week time spent in: direct service (vs. indirect)—the community (vs. in the office)—Collaborating with mental health clinicians in the clinic—Job development—Job support

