#### Secondary participant-centered outcomes

These outcomes will capture individual-level changes related to employment, financial stability, and health. A detailed schedule of assessments is presented in Table 3.Employment outcomes: monthly employment status (employed/not employed), job start and end dates, average hours worked per week, and hourly wages.Financial well-being: annual income, income sources, and housing stability over the past 12 months.Health-related outcomes: use of health services (e.g., hospitalizations, emergency visits) and self-reported measures of general health and functioning.

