### Data collection and management

#### Plans for assessment and collection of outcomes

Baseline structured interviews will be conducted prior to randomization to collect data on demographic characteristics, social capital, physical and mental health status, health service utilization, justice system involvement, functionality, and employment and financial history [21]. Validated instruments with established psychometric properties and Spanish versions will be used at baseline and follow-up assessments. These include the Brief Psychiatric Rating Scale (BPRS) for psychiatric symptoms [22], the Medical Outcomes Study Short-Form 12-Item (SF-12) for physical and mental health [23], the Social and Occupational Functioning Scale (SOFS) for functioning and role performance [24], and the Recovery Assessment Scale (RAS-24) to assess perceived recovery and empowerment [25]. All instruments will be administered by trained research staff using structured protocols to ensure consistency and data quality.

Quarterly structured follow-up interviews will assess employment status during the prior 3 months. Data collected will include job titles, employment dates, hours worked, and wages earned. When applicable, the reason and timing of job termination will also be recorded [21]. These structured interviews will be conducted in person at the Center for Comprehensive Care in Long-Stay Mental Health, subject to public health restrictions. If a participant is unavailable, the research team will make multiple contact attempts within the same data collection window. Missed interviews will be documented, and retrospective data will be gathered at the next opportunity.

Follow-up structured research interviews scheduled at 6- and 12 months after randomization, the follow-up interviews will augment the quarterly employment interviews and include measures of health and functionality mirroring those administered at baseline. Additional data collected describes housing, social capital, and health service utilization [21]. Follow-up interviews will be conducted at the same time as the corresponding quarterly employment interviews. As with the quarterly employment interviews, when participants are unavailable for follow-up interview, the research assistant will make several efforts to track and schedule the interview within the designated time until the next quarterly interview period.

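### Table 3 words the quarterly interview, the only listed follow-up source of earnings, around competitive jobs with an hourly wage; other sections set no such limit, and the work typical of usual care may be missed

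*Protocol article*

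**What the plan says.** All references are to the Protocol article.

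- **Outcomes, Table 3, quarterly interview:** "Past-quarter employment (any competitive employment; per-job weeks worked, hours worked per week, hourly wage, job start/end dates if applicable". The article presents this table as its full listing of outcomes and measures.
- **Secondary participant-centered outcomes, employment:** "monthly employment status (employed/not employed), job start and end dates, average hours worked per week, and hourly wages". Nothing here confines employment to competitive jobs.
- **Plans for assessment and collection of outcomes, same quarterly interview:** "Data collected will include job titles, employment dates, hours worked, and wages earned". Again there is no competitive limit, and the item is wages earned rather than an hourly rate.
- **Secondary participant-centered outcomes, finance:** "Financial well-being: annual income, income sources, and housing stability over the past 12 months".
- **Outcomes, Table 3, baseline interview:** "income history (annual income, income sources". The 6- and 12-month interview lists housing, service use, health and functioning, but no income item. The data-collection section does not add one.
- **Explanation for the choice of comparators:** "The positions offered through these channels are generally categorized as non-competitive or self-employment activities, such as broom-making, craft-making, or gardening". By contrast, the Intervention description directs the IPS specialists towards competitive openings.
- **Eligibility criteria:** "having no competitive employment in the past 3 months". A person already in cooperative or self-employed work can therefore be enrolled in either arm.

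**The concern.** Competitive employment is a proper endpoint for an IPS trial, and nothing here argues against it. The difficulty is earnings. Broom-making, crafts or gardening done through a cooperative or on one's own account is not competitive work as the article uses the term, and it may not be paid by the hour. An interviewer working from Table 3 could leave such a job out, while one working from the data-collection section would enter it. Since this is the kind of work usual care tends to offer, whatever is left out may differ between arms. Blinding the interviewers does not cure that, because the omission comes from the content of the form and not from the interviewer's judgement.

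The Statistical methods section will model financial well-being and report effect sizes with 95% confidence intervals, and the Trial design section says the pilot's estimates will be used to plan a later regional trial. An arm-related measurement error would be carried into that planning.

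**Working it through.** The documents state no earnings figure, so there is none to reproduce. The check has two parts.

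**1. Which instrument can measure earnings after baseline?**

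| Source | Timing | Income or earnings content |
|---|---|---|
| Baseline interview | Baseline | Annual income, income sources |
| Quarterly employment interview | Quarterly | Per-job weeks, hours and hourly wage (Table 3); wages earned (data-collection section) |
| Follow-up interview | 6 and 12 months | None listed |
| IPS Participation Measure | Monthly, completed by the specialists for their own clients | Competitive employment status only, no earnings |

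The housing component of financial well-being is followed up; the income component is not. The Aims and objectives nevertheless plan to compare financial outcomes at baseline, 6 and 12 months. As listed, any follow-up earnings must come from the quarterly record, so its scope decides what the financial comparison can show.

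**2. What would a competitive-only record do to the comparison?**

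Let p be the proportion in competitive work (earning 100 units) and q the proportion in other paid work (earning w units), with subscripts I for IPS and C for control.

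- Recorded difference = 100 × (p_I − p_C)
- All-work difference = recorded difference − w × (q_C − q_I)

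The error therefore equals control-arm minus IPS-arm earnings from non-competitive work. Its sign follows the sign of that gap.

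Illustration only. p_I = 55% is the rate the Background reports from high-income countries. p_C = 25%, w = 20 to 80 and every q are assumptions. The recorded difference is 100 × (0.55 − 0.25) = 30.

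| q_C v q_I | All-work difference, w = 20 | w = 50 | w = 80 | Recorded ÷ all-work |
|---|---|---|---|---|
| 10% v 10% | 30 | 30 | 30 | 1.00 |
| 20% v 10% | 28 | 25 | 22 | 1.07 to 1.36 |
| 40% v 10% | 24 | 15 | 6 | 1.25 to 5.0 |
| 10% v 20% | 32 | 35 | 38 | 0.94 to 0.79 |

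For example, 40% v 10% at w = 50 gives 30 − 50 × (0.40 − 0.10) = 15, so the recorded difference is twice the all-work one. The range runs from none to large, and the last row goes the other way.

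**The case against.** The strongest reply is that Table 3 is a condensed list. Its semicolon can be read as separating a competitive-employment item from details taken for every job, and two other sections describe the same content without restriction. The interview form is cited but not shown, and an article may leave form content to the full protocol. This stands in part: the text is inconsistent rather than plainly restrictive. It does not remove the need to settle which reading applies.

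Second, financial well-being is defined by annual income and income sources, which would include earnings of any kind, and not by the quarterly wage record. That is correct as a definition. It would answer the concern if those items were listed after baseline, and they are not.

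Third, baseline income and employment history would capture earlier cooperative work, so a move from a cooperative to a competitive job need not appear as pure gain. That also stands, although baseline and follow-up would then be measured on different bases.

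Fourth, both arms keep standard mental health services and every participant wants competitive work, so non-competitive earnings might not differ by arm. The documents do not exclude this.

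A reader might go further and infer that control-arm earnings will go unmeasured and that the IPS financial benefit will be overstated. The documents do not support either statement as fact. The first requires the narrow reading of Table 3; the second also requires more non-competitive earnings in the control arm, for which no figures are given.

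**Conclusion.** The point holds as an inconsistency to be resolved, together with a gap in the follow-up schedule. Under the narrow reading of Table 3, earnings from non-competitive or self-employed work may be missed. The financial comparison would favour IPS if such earnings are more common in the control arm. The descriptions of the two arms make that the more plausible direction, but they do not quantify it. The multiples worked out above rest on assumed rates and pay; no magnitude can be derived from the documents.

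The weight is moderate. The outcomes affected are secondary and exploratory, the trial was not powered on them, and none enters the progression criteria. The change is still worth making because it is cheap now and because earnings not asked about during follow-up would be hard to recover later.

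**What to change.** 1. Reconcile Table 3 with the employment outcome list and the data-collection section, so that the quarterly interview records every paid activity in both arms: competitive, cooperative or sheltered, and self-employed.
2. Give each job a competitive yes/no flag, and add total earnings for the quarter alongside the hourly wage, so that piece-rate and self-employed income can be entered.
3. Add annual income and income sources to the follow-up interview, at 12 months at least, in the same form as at baseline.
4. State that employment is analysed on competitive jobs and financial well-being on income from all paid work.

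The cost is a few fields on existing forms, one of which is a 10-minute interview, and a slightly longer visit. The apparent financial effect may turn out smaller. The Trial status section says recruitment has not begun, so all participants could be measured in the same way from the start.
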